**Fig 1 pone.0275357.g001:**
[figure not shown]
The study timeline. • the time points; Mo: month.

Fig 2 shows the CONSORT flow diagram of the present study protocol.

**Fig 2 pone.0275357.g002:**
[figure not shown]
CONSORT diagram of the study flow.

### Ethics approval and consent to participate

Ethical approval was obtained from the Ethics Committee for Research Involving Human Subject (JKEUPM) of Universiti Putra Malaysia (Reference no: JKEUPM-2020-349) on 20 December 2020. Permission to conduct the study in the flats was obtained from Kuala Lumpur City Hall and management office of the selected PPR flats. The written informed consent will be obtained from the participants. The study was registered at ClincalTrials.gov (Identifier: NCT04688515) on 29 December 2020.

The purposes of the study will be explained by the researcher to the participants as well as the procedures to be performed, their discomforts and risks, and the guarantees of confidentiality. The participants will voluntarily agree to participate in this study and will be able to withdraw consent at any time, before or during it, without any penalty. There is minimal risk in this study. The only concern is the food safety issue during the cooking demonstration session in the intervention group. However, by taking precautions such as providing fresh ingredients, washing hands and wearing necessary protective coverings, the possible risk can be reduced. Moreover, mothers will also be reminded to notify the researcher if their children experience discomfort or show symptoms such as vomit and diarrhoea after consuming the meals provided in the program. The child will be taken to the nearby clinic or hospital as soon as possible for further treatment.

### Data monitoring

Investigators from the Department of Nutrition will be involved in the design and the implementation of the interventions. The principal investigator will be responsible for supervising the administrative management of the study and the execution of the trial, record keeping and data management. This study will evaluate the nutrition programme using positive deviance approach that is highly unlikely to be related to serious adverse events. Thus, no data monitoring committee or auditing will be needed. However, the principal investigator will take care of monitoring and will be responsible for the progress of the study.

### Potential amendments

The recruitment of participants is scheduled to be carried out in 2022. Phase 1 of study (FGD) is expected to be carried out from February to June 2022 and Phase 2 (RCT) is expected to start in September 2022. To date, the recruitment of participants for Phase 1 has begun and is on-going. However, this might be temporally suspended as a response to controlling the COVID-19 pandemic in the country and that would affect the project timeline. In case a need for modification should arise, it will be registered and reported in this journal.

### Statistical analysis

All data collected will be entered and analysed by using IBM SPSS Statistics 26 (SPSS Inc., Chicago, IL, USA). The normality distribution of data will be tested by evaluating the values for skewness and kurtosis between -2 and +2 [47]. The differences in anthropometric measurements (WAZ, HAZ, WHZ), dietary practices (energy, macronutrient and micronutrient intakes, diet quality and consumption of the promoted foods) of children, food security status, and nutritional knowledge of mothers between intervention and comparison groups at baseline (before intervention), immediate post-intervention, and 3-month post-intervention will be tested using the independent-samples t-test and repeated measure ANOVA. Furthermore, Generalised Linear Models (GLM) will be performed to evaluate the effectiveness of the programme. All p-values are two-tailed and the level of significance will be set at p<0.05 and post-hoc adjustment will be performed for multiple comparisons. All data will be treated following an intention-to-treat approach and multiple imputation will be used for treating missing data whenever possible.

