### Study design

This is a mixed-method study that involves both qualitative and quantitative methods. In phase one of the study, a qualitative research method will be used while in phase two, a two-armed cluster RCT will be conducted. The primary outcome of the RCT study will be weight-for-age z-score (WAZ), while the secondary outcomes will include height-for-age z-score (HAZ), weight-for-height z-score (WHZ), nutrient intake, diet quality, food security status and nutritional knowledge of mothers. The study population includes 3 to 5 years old children with their mothers who live together in the low-cost PPR flats in Kuala Lumpur. Children aged 3 to 5 years old are recruited because when compared to younger children (<2 years old), older children are at higher risk of undernutrition [32].

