### Sample size estimation

Sample size will be calculated using the formula for a RCT comparing two groups of equal size [37, 38], two-tailed test with 80% power and 5% significance level. As there was minimal information on the nutritional status of urban poor children and the effectiveness of nutrition programme in the setting of Malaysia, this study used the information obtained from a previous study that was not done in Malaysia but was using PD approach and it is relevant to the context of the present study [25]. By referring to the mean and SD of the WAZ of children aged 36 to 48 months in the intervention (using the PD approach) and comparison groups from a previous study [25], the minimum sample size required will be 28 in each group. It is estimated that there are around 10 households with undernourished children under five in a cluster of PPR flat. Thus, the cluster size per arm, m, is assumed to be 10 and the intra-cluster correlation coefficient (ICC) is assumed to be 0.03 [39]. Hence, with a calculated design effect of 1.27 and a non-response rate of 20%, the sample size is increased to 41 in each group.

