### Measurements

All the measurements in the study will be taken at the baseline, immediate post-intervention, and 3-month post-intervention for both intervention and comparison groups. A Malay language self-administered questionnaire on sociodemographic characteristics, nutritional knowledge, and food security status will be answered by mothers. The sociodemographic background of the mother-child dyads will be self-reported by the mothers, including information on both the child and the mother.

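### WAZ, the primary outcome, is given visit-wise t-tests, repeated-measures ANOVA and GLM, with no primary visit or method and no stated adjustment for baseline WAZ

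*Protocol article*

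**What the plan says.** All references are to the protocol article.

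- **Study design:** "The primary outcome of the RCT study will be weight-for-age z-score (WAZ"; the sentence then lists the secondary outcomes. It gives no time point for WAZ.
- **Measurements:** "All the measurements in the study will be taken at the baseline, immediate post-intervention, and 3-month post-intervention". There are therefore two follow-up visits at which WAZ could be judged.
- **Statistical analysis:** group differences in all outcomes, WAZ among them, "at baseline (before intervention), immediate post-intervention, and 3-month post-intervention will be tested using the independent-samples t-test and repeated measure ANOVA". The section then says that "Generalised Linear Models (GLM) will be performed to evaluate the effectiveness of the programme". It names no covariate, outcome form or visit for these models, and it ranks none of the three methods.
- **Statistical analysis, on multiplicity:** "the level of significance will be set at p<0.05 and post-hoc adjustment will be performed for multiple comparisons". It gives neither the procedure nor the family of tests.
- **Sample size estimation:** a "two-tailed test with 80% power and 5% significance level", in a plain two-group comparison of mean WAZ. No baseline or correlation term is described.

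**The concern.** Three things follow from the text as written.

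1. **No deciding test.** WAZ has two follow-up visits and three methods, and repeated-measures ANOVA itself yields more than one test of the arms. These can disagree on the same data, and no rule says which one answers the primary question.
2. **Baseline WAZ is measured but not clearly used.** A t-test on follow-up values ignores it, so a chance baseline imbalance passes straight into the result. The ANOVA group main effect includes the baseline visit, where the programme cannot yet have acted, and so dilutes the effect.
3. **A significance test at baseline** says nothing about the programme.

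At stake are the error rate of the claim that the programme works, and precision in a trial of only 82 children.

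**Working it through.** **Inputs from the article.** Two-sided alpha 0.05, power 0.80, 28 per arm before inflation, 41 per arm after it, three visits, ICC 0.03, seven flats per arm.

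**Assumptions, not in the article.** The correlation r between WAZ at any two visits is equal across pairs and lies between 0.5 and 0.9. Where an effect exists, it is the same at both follow-up visits.

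**The plan's own figure.** The mean and SD behind "the minimum sample size required will be 28 in each group" are not printed, so 28 cannot be recomputed. It can be inverted: d = (1.960 + 0.842) × √(2/28) = 0.749 SD.

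**Step 1: precision lost by a follow-up t-test.** Adjusting for baseline (ANCOVA) multiplies the variance by 1 − r². The detectable difference at 28 per arm becomes 0.749 × √(1 − r²).

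| r | share of variance unused (r²) | 1 − r² | detectable difference, adjusted (SD) |
|---|---|---|---|
| 0.5 | 25% | 0.75 | 0.65 |
| 0.7 | 49% | 0.51 | 0.54 |
| 0.8 | 64% | 0.36 | 0.45 |
| 0.9 | 81% | 0.19 | 0.33 |

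The unused share passes one half only when r exceeds √0.5 = 0.71.

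**Step 2: dilution of the ANOVA group main effect.** The effect is present at two of three visits, so the averaged difference is 2d/3. The SD of a child's three-visit mean is √((1 + 2r)/3). The standardised effect is therefore d × (2/3)/√((1 + 2r)/3), which is 0.82d at r = 0.5 and 0.69d at r = 0.9.

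**Step 3: how far the tests differ.** Simulated power, 28 per arm, no clustering, 8,000 runs. Each cell gives power at d = 0.749, then at half that effect.

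| r | t-test, one visit | ANOVA group effect | ANOVA group-by-time | ANCOVA, one visit |
|---|---|---|---|---|
| 0.5 | 78% / 28% | 60% / 20% | 81% / 28% | 88% / 35% |
| 0.7 | 79% / 28% | 54% / 17% | 97% / 44% | 97% / 48% |
| 0.8 | 78% / 29% | 51% / 17% | >99% / 61% | 99% / 63% |
| 0.9 | 79% / 28% | 47% / 16% | >99% / 90% | >99% / 88% |

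The group-by-time term is close to ANCOVA at r = 0.8 to 0.9. The t-test and the group main effect are not.

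**Step 4: chance of at least one false p<0.05 for WAZ.** No true effect, 41 per arm, no clustering, no multiplicity correction, 20,000 runs.

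| r | two follow-up t-tests | plus both ANOVA terms | plus a baseline-adjusted GLM at each follow-up |
|---|---|---|---|
| 0.5 | 9.4% | 14.1% | 16.6% |
| 0.7 | 8.3% | 13.0% | 16.2% |
| 0.8 | 7.2% | 12.0% | 15.7% |
| 0.9 | 7.0% | 11.6% | 15.7% |

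Allowing for simulation error, this is about 11 to 15% for the tests the article names, and 15 to 17% with the adjusted GLMs. If the children also share flats (ICC 0.03, seven flats per arm) and the analysis ignores it, the last column rises to about 20 to 22%.

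**The case against.** **The plan as a whole wastes most of its precision.** A reader might infer this, and the documents do not support it. The repeated-measures ANOVA includes the baseline visit, so its group-by-time term uses within-child change and nearly matches ANCOVA at r = 0.8 to 0.9. The loss belongs to the t-tests and the group main effect. For the t-tests it is more than half only if r exceeds about 0.71. No r is given, and enrolling only undernourished children may lower it. The article does not, however, say that the group-by-time term is the test. That term is also a joint test over visits and gives no effect estimate at a named one.

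**The plan's type I error is 16 to 21%.** This does not follow either. Those figures include two baseline-adjusted models that the article does not specify, and the upper end also includes the separate effect of ignoring flats. All the error figures assume no correction, while the article promises one. What stands is that the promise has no method or scope, and such wording ordinarily covers pairwise contrasts rather than a choice among t-test, ANOVA and GLM.

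**Repeated-measures ANOVA breaks intention-to-treat by dropping incomplete children.** The article plans multiple imputation whenever possible, so no contradiction is shown.

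**This is detail for an analysis plan not shown.** In part this is fair. The GLM covariates are unstated, so baseline adjustment is neither planned nor excluded, and the GLM sentence can be read as marking the effectiveness analysis. But the article is not silent. It commits to between-arm testing of the primary outcome by t-test at every visit and by ANOVA as well, and that commitment would have to change whatever a later plan adds.

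**Conclusion.** The point holds in a limited form. The article commits to overlapping tests of WAZ, including one at baseline, without saying which visit and method decide and without stating a baseline adjustment.

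- **Precision:** the follow-up t-tests leave 25 to 81% of the variance unused over r = 0.5 to 0.9. The ANOVA group main effect is weaker still; the group-by-time term is not affected in this way.
- **False positives:** about 11 to 15% for WAZ from the named t-tests and ANOVA terms if left uncorrected, and higher if clustering is ignored. This describes what happens if any of those tests may be claimed; it is not a fixed property of the plan.

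These sizes rest on the assumed r, on equal correlation between visits and on no multiplicity correction. The absence of a deciding visit and method rests on the text alone.

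**What to change.** Before Phase 2 data are seen:

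1. Name one follow-up visit as primary, for example immediate post-intervention. The documents do not favour either visit, so this is the investigators' choice.
2. Name one primary analysis: the between-arm difference in WAZ at that visit, adjusted for baseline WAZ, in a model that accounts for flat. Age and sex are optional covariates, since WAZ is already standardised for both.
3. Report the other follow-up visit from the same model as secondary.
4. Make the t-tests and repeated-measures ANOVA descriptive or supportive only, and drop the baseline significance test.
5. State which comparisons the post-hoc adjustment covers and by what method.

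Cost: wording and minor analysis work. Baseline WAZ is already collected, and no participants or visits are added. The Potential amendments section provides for modifications to be registered and reported. The downside is that one pre-specified result replaces several, so a favourable result at the other visit or from another test could no longer carry the main claim.

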### Implementation of intervention

For the intervention group, a nutrition programme consisting of an education session with peer-led cooking session and rehabilitation session will be provided. The programme will be known as the Nutrition Education and Rehabilitation Session (NERS). It is planned as a 3-month intervention with a total of 12 sessions, each session lasting for two hours for one day in a week, making up a total of four days in one month. The two-hour session consists of half-an-hour of education lesson followed by one and a half-hour of peer-led cooking session. The rehabilitation session will constitute the remaining days before the next education session. The overall education session will be conducted by the researcher. However, the cooking session will be led by volunteers who are recruited from the PD families in the initial stages of the study. Peer-led cooking session will encourage the involvement and active interaction from the volunteers to assist participating mothers in the food preparation processes for child feeding. The participating mothers will need to bring along their undernourished children during this session and feed their children with the prepared meals when they finish cooking. During the process, volunteered mothers from PD family are encouraged to share their knowledges of preparing food and child feeding to the participating mothers to enhance the PD effect. Five to six mothers will be assigned in a group to prepare meals for five to six children. Each group will be assigned with one volunteer to help them throughout the process. Fresh ingredients will be provided. The meal in each cooking session will be prepared according to the pre-planned NERS menu and will be fed as a snack or additional meal to children. This programme will also include a growth monitoring session whereby the participating mothers weigh their children during each session of NERS before the start of the education session. A weighing scale will be provided by the researcher. Mothers will be trained to weigh their children so that they can monitor their children’s nutritional status.

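### Repeated-measures ANOVA with only conditional imputation leaves a completer analysis open under an intention-to-treat claim

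*Protocol article*

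**What the plan says.** The Statistical analysis section lists the anthropometric, dietary, food-security and knowledge outcomes at baseline, immediately after the programme and three months later. It says that group differences "will be tested using the independent-samples t-test and repeated measure ANOVA". Generalised Linear Models are then added to evaluate effectiveness. On missing data it says "All data will be treated following an intention-to-treat approach and multiple imputation will be used for treating missing data whenever possible". No other missing-data rule is given.

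Three other places bear on this:

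- Study design names WAZ as the primary outcome.
- Sample size estimation works "with a calculated design effect of 1.27 and a non-response rate of 20" per cent to reach 41 per group.
- Measurements schedules all assessments at all three visits in both groups.

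**The concern.** Intention-to-treat means that every randomised child counts in the arm to which it was allocated. Classical repeated-measures ANOVA works on complete rows, so a child with baseline and end-of-programme weights but no final weight contributes nothing, not even the two values that were measured. Imputation would prevent this, but the plan commits to it only where it turns out to be feasible and does not say who decides, when, or by what rule. The analysed set can therefore be settled after the data have been seen.

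At stake is the WAZ comparison, above all at the last visit, which tests whether any gain persists. The children lost may differ from those kept, and the arms carry different demands. For the intervention arm, "It is planned as a 3-month intervention with a total of 12 sessions, each session lasting for two hours", while the comparison arm has only the measurement visits.

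**Working it through.** **1. The plan's own figure.** Inputs from Sample size estimation: 28 per group before adjustment, cluster size 10, ICC 0.03, non-response 20%.

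- Design effect = 1 + (10 − 1) × 0.03 = 1.27, as stated.
- Adding both allowances to one gives 28 × (1 + 0.27 + 0.20) = 41.16, which matches the stated 41.
- Applying them in turn gives 28 × 1.27 = 35.56, then 35.56 × 1.20 = 42.67 or 35.56 / 0.80 = 44.45. That difference is a separate sample-size matter and is not used here.

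**2. Children left per arm if incomplete rows are deleted.**

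- All losses in the same children: 41 × 0.80 = 32.8, about 33.
- 20% missing independently at each of the two follow-up visits (assumption): 41 × 0.80 × 0.80 = 26.2, about 26.
- In the second case, children with baseline and at least one follow-up number 41 × (1 − 0.20 × 0.20) = 39.4. A model that uses every available visit keeps about 13 children per arm that the ANOVA discards (39.4 − 26.2 = 13.2).

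**3. Bias from deletion at the last visit.** The documents give neither loss by arm nor the WAZ of children who leave, so these inputs are assumptions: 20% of one arm lost after the end-of-programme visit; odds of loss 1.5 to 3 times higher per SD lower WAZ at that visit; correlation between that visit and the last of 0.7 to 0.9. A simulation with bivariate normal values and logistic loss gave:

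| Correlation | Odds ratio per SD | Shift in completers' mean | After regression on the observed earlier visit |
|---|---|---|---|
| 0.7 | 1.5 | about 0.06 SD | about 0 |
| 0.9 | 3 | about 0.17 SD | about 0 |

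The last column shows that deletion causes this bias. When loss depends only on WAZ already measured, using the measured visits removes it.

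**4. Direction.** A second simulation assumed a true effect of about 0.75 SD (roughly what 28 per group at 80% power implies), a baseline to follow-up correlation of 0.8, and loss in the intervention arm that depends on baseline WAZ.

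| Who leaves the intervention arm | True effect | Complete cases | Imputed from observed baseline, by arm |
|---|---|---|---|
| Mainly the lightest | 0.746 | 0.91 | 0.747 |
| Mainly the heaviest | 0.746 | 0.58 | 0.746 |

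Deletion errs either way; use of the observed values does not err here.

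**5. Where missing-at-random methods also fail.** Let p be the share of the intervention arm lost and r the share of the benefit that those children keep. Methods that fill or model them like the children who stayed overstate the all-randomised effect by 1 / ((1 − p) + p × r) − 1.

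- p = 0.20, r = 0: 1 / 0.80 − 1 = 25%.
- p = 0.20, r = 0.5: 1 / 0.90 − 1 = 11%.
- Any p, r = 1: 0%.
- p = 0.30, r = 0: 1 / 0.70 − 1 = 43%.

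In simulation with p = 0.20 and r = 0, the true effect was 0.60, the by-arm imputation gave 0.75, and imputation from the comparison arm gave 0.60. With r = 0.5 the true effect was 0.67 and comparison-arm imputation again gave 0.60. It is thus a cautious bound and not a correction.

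**The case against.** The strongest reply is that the plan pairs the ANOVA with multiple imputation. If every missing visit is imputed, no child is dropped, and the ANOVA and the intention-to-treat claim do not contradict each other. That stands. The fault lies in the conditional wording, which leaves deletion as the fallback.

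It can also be said that the Generalised Linear Models are the effectiveness analysis and may use every visit, and that the t-tests do not need all three. This weakens the point without removing it. The models are introduced as an addition, are not named as primary, and are not said to use repeated visits. An ordinary generalised linear model on stacked visits would ignore the correlation within a child.

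Three stronger readings are tempting, and the documents support none of them:

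- **That the plan imputes children who leave as if they had continued the programme.** No imputation model is stated. That property belongs to one possible model, and the choice of model is a detail that an article commonly leaves to the full protocol or analysis plan.
- **That the effect is therefore overstated.** Step 4 shows error in both directions, and step 5 ranges from 0% to 43% on assumptions alone. Which arm will lose more is unknown: the intervention arm has the sessions, but it also receives ingredients and meals, and the Comparison group section worries about dropout from that group.
- **That a mother who stops the sessions stops being measured.** The ethics section says only that participants "will be able to withdraw consent at any time, before or during it, without any penalty", and Measurements plans every visit for both groups. Nothing ends measurement when attendance ends.

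**Conclusion.** The concern holds as a badly fixed rule, not as demonstrated bias. As worded, the plan allows the WAZ test to become a completer analysis on about 33 of 41 children per arm at its own 20% loss, or about 26 if the missed visits fall on different children. Under the stated assumptions the bias at the last visit is about 0.06 to 0.17 SD. Its sign depends on who leaves and from which arm, and it is about zero once the observed visits are used and loss depends only on them. Loss by arm and its relation to WAZ are assumed throughout, because the article does not give them. A better and inexpensive method exists, so the change is worth making before data collection.

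**What to change.** In the Statistical analysis section:

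1. For WAZ, replace the repeated-measures ANOVA with a likelihood-based longitudinal mixed model that uses every available visit from all randomised children in their allocated arm.
2. Delete the words *whenever possible*, so that the handling of missing data is a fixed rule.
3. Because the mixed model also assumes data missing at random, add one sensitivity analysis for WAZ in which missing intervention-arm values are imputed from the comparison arm. Present it as a cautious bound beside the main estimate.

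The cost is a few lines of text and a little more programming in standard software. The estimate may come out less favourable to the programme. No extra visits or participants are needed.
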